### 3.4. Randomization and Blinding

A statistician not involved in data collection will use SPSS to randomly assign participants, with the results enclosed in sealed envelopes. After baseline assessment, envelopes will be opened, and group assignments (experimental or active control) will be disclosed to the interventionist via phone only.

Double blinding will be employed for data collectors and participants. Participants will be blinded through a sham treatment (see below), and data collectors will not have access to group assignments. To assess the effectiveness of the blinding, data collectors will be asked two questions at the start and conclusion of the study: “Are you aware of the interventions in this study?” and “Can you identify whether the participant was in the experimental or control group based on any clues?” Participants will also answer two questions: “What guidance did you receive during the study?” and “Do you think you were in the experimental or active control group?” These questions will help evaluate the success of the blinding process.

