### 3.5. Intervention and Sham Treatments

#### 3.5.1. Experimental Group: Intervention

The intervention comprises the interactive podcast program, “Living with Type 1 Diabetes to Grown-Up,” which includes podcast episodes and interactive voice feedback. The program features 36 episodes, released at a rate of three per week over a 3-month intervention period [65]. Based on pilot testing for optimal duration and speech rate [56], each episode lasts 8–15 min with a word count of 160–220 words per minute. The content incorporates participant recommendations and uses appropriate language, presented lightly and engagingly. The topics and subtopics are detailed in Table 1. In addition to episode ratings and encouraged comments, participants will provide voice feedback aligned with the objectives and content of each unit to enhance practical application. During the first 9 weeks of the intervention, every 3 weeks (at Weeks 3, 6, and 9), participants will select a topic from the podcast episodes they have completed and provide voice feedback based on the PRIDE interactive voice feedback protocol and steps, as detailed in Table 2. The principal investigator will then coordinate expert responses tailored to participants' feedback, delivered in the following weeks 4, 7, and 10. Each participant will engage in three personalized voice feedback interactions over the study period, and all feedback will be thoroughly documented to assess TF through content checking, ensuring accurate implementation and alignment with participant needs. While episodes cannot be downloaded, participants can listen to them again throughout the intervention.

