#### 3.7.2. Primary Outcome: Wellbeing—Disease Control Outcomes

Assessed through HbA1c, the percentage of self-monitored blood glucose readings within the 70–180 mg/dL range, the number of hypoglycemic events (blood glucose < 70 mg/dL), and the number of hyperglycemic events (blood glucose > 180 mg/dL) [70] will be noted. HbA1c will be recorded from electronic medical records after blood samples are collected during patient visits. The percentage of self-monitored blood glucose readings within the 70–180 mg/dL range will be calculated using the formula: (number of values within the 70–180 mg/dL range/total number of tests)∗100% [57].

A data downloader at outpatient clinics will be used to retrieve the past 3 months' blood glucose data and reset it to prevent data from overlapping or being overwritten. Subsequently, two data collection assistants will simultaneously review the data manually. If discrepancies arise, the principal investigator will verify the data. Finally, interrater reliability will be assessed using Cohen's Kappa coefficient to ensure consistency in their evaluations [71]. In cases of abnormal blood glucose values, such as hypoglycemia, if the participant follows up with a blood glucose check 15 min after consuming carbohydrates, only the first recorded value (i.e., the pretreatment blood glucose value) will be used for analysis. Commercial blood glucose meters can store 500–1000 data points, and participants typically measure 2–5 times daily. Therefore, based on prior studies, data coverage is not expected to be an issue [57].

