The second	After listening to Weeks 4–6, what are the main issues in stress management, behavior control, genetic knowledge, or future planning? How do these issues affect your health management?	Reflect on the past 3 weeks and apply program knowledge, such as stress, substance use, diabetes and sexuality, and uncertain future, to review your daily activities and identify the root causes of the main issues.	Based on Weeks 4–6 of learning, set specific health management goals to address the issue.	List and apply strategies learned from the program, such as stress management, to develop a plan for achieving your goals.	Establish a new reward system for achieving your goal. For example, if I practice bedtime meditation and go to bed on time for three consecutive weeks, I will reward myself with a concert.	Did you achieve your goal? Reasons for success or failure?

Self-verification (check and upload)						
The third	After listening to Weeks 7–9, what are the main issues in disease disclosure, interpersonal relationships, communication, and emotional distress? How do these issues affect your disease management?	Reflect on the past 3 weeks and apply program knowledge, such as concerns about interpersonal communication, common causes of family conflict, and resulting emotional distress, to identify the root causes of the main issues.	Based on Weeks 4–6 of learning, set specific health management goals to address the issue.	List and apply strategies learned from the program, such as stress management, to develop a plan for achieving your goals.	Establish a new reward system for achieving your goal. For example, if I achieve my planning and communication goals for these 3 weeks, I will reward myself with a relaxing trip.	Did you achieve your goal? Reasons for success or failure?

Self-verification (check and upload)						

**Table 3 tab3:** The intervention characteristics between the experimental group and active control group.

**Key differences in intervention**		**Experimental group (intervention)**	**Active control group (sham treatment)**
Intervention modality	Voice media	V	—
	Text-based E-book	—	V

Interaction	Voice feedback and response	V	—
	No interaction	—	V

Intervention topics	Knowledge	V	V
	Exercise and diet	V	V
	Interpersonal relationships	V	V
	Parent-child relationships	V	V
	T1D and COVID-19	V	—
	Sleep	V	—
	Stress	V	—
	Risk behaviors	V	—
	Sexuality and genetics	V	—
	Employment and career	V	—
	Transition to adult healthcare	V	—

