Intervention mechanism	Behavior modification (PRIDE framework)	V	—
	Peer experience share	V	—
	Personalized professional guidance	V	—

Intervention contact	Phone contact at 1.5 months of intervention	V	—

**Table 4 tab4:** The strategies of treatment fidelity.

**Dimensions**	**Strategies**	**Contents**	**Target population**		
			**Research assistants**	**Experimental group (intervention)**	**Active control group (sham treatment)**
Treatment design	1.「Standard manual for experimental and active control groups」	(1) Study objectives and standardized data collection process	RA_1_	—	—
		(2) Study objectives and standardized intervention details, intervention implementation process, and interaction	RA_3_	—	—
	2. 「Experimental group and active control group checklist for intervention steps」	Audit and ensure the completeness and fidelity of interventions conducted by RA_1_ and RA_3_.	RA_2_&RA_4_	—	—

Training provider	1.「Research assistant training manual」	(1) Training by the PI for 40 h (2) Challenges and management of T1D patients in transition (3) Study protocol, execution methods, intervention or data collection procedures, considerations, and ethical issues (4) Communication and interaction skills	RA_1-4_	—	—
	2. Clinical shadowing training	(1) Observation: two clinic shadowing sessions for familiarization and demonstrations by experienced graduate students (2) Practice: the first 10 participants are handled with PI's support and discussion	RA_1-4_	—	—

Delivery of treatment	1. Concurrent data collection and intervention implementation by two research assistants	(1) Conduct data collection (RA_1_) or intervention implementation (RA_3_) according to the “standard manual” (2) Intervention audit according to the “checklist for intervention steps “by RA_2_ and RA_4_	RA_1-4_	—	—
	2. Intervention process analysis	Audio recordings of all sessions and analysis randomly by the PI	RA_1-4_	—	—
	3. Regular discussions	Logs for recording issues during data collection and intervention implementation; weekly discussions with the PI [69]	RA_1-4_	—	—

Receipt of treatment	1. Field discussion	Discussions and clarifications with participants during interventions	—	V	V
	2. Teach back	Participants demonstrate the intervention and receive feedback	—	V	V
	3. Intervention content checklist for participant	Participants confirm receipt of all intervention components after completion	—	V	V

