Enactment of treatment skill	Random follow-up	Monthly random follow-up with 5 participants, analyzing login and feedback records to ensure implementation in daily life [69]	—	V	—

Abbreviations: RA_1_, Research Assistant 1, responsible for data collection; RA_2_, Research Assistant 2, supervising the data collection process; RA_3_, Research Assistant 3, responsible for intervention implementation; RA_4_, Research Assistant 4, auditing the implementation of interventions.

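### The principal investigator can identify the experimental arm through the feedback role, yet settles disputed self-monitored glucose data, so those primary-outcome records are not assessed blind

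*Protocol article*

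**What the plan says.** **Blinding.** Section 3.4 of the protocol article states: "Double blinding will be employed for data collectors and participants". It adds that "data collectors will not have access to group assignments" and that assignments "will be disclosed to the interventionist via phone only". Sections 3.1 and 4.1 call the trial double-blind, and Section 4.1 presents this among the strengths of the evaluation.

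**Glucose data.** Section 3.7.2 lists four primary measures: HbA1c, the percentage of self-monitored readings between 70 and 180 mg/dL, the number of readings below 70, and the number above 180. The last three come from meter downloads that two assistants review manually, with agreement summarised by Cohen's kappa. On disagreement: "If discrepancies arise, the principal investigator will verify the data". Where an abnormal value is followed by a repeat check after carbohydrate, only the first value counts.

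**The investigator's part in the intervention.** Section 3.5.1: "The principal investigator will then coordinate expert responses tailored to" what participants say in their voice feedback. Replies go out in Weeks 4, 7 and 10. In Table 3 the row "Voice feedback and response" is ticked for the experimental group and dashed for the control group. Table 4 also has the investigator analyse randomly chosen session recordings and support the handling of the first 10 participants.

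**Research assistants.** The body of Table 4 names RA2 and RA4 together for the task "Audit and ensure the completeness and fidelity of interventions conducted by RA_1_ and RA_3". The footnote gives separate roles: "Research Assistant 2, supervising the data collection process" for RA2, and auditing of the interventions for RA4.

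**The concern.** Blind assessment protects an outcome only if whoever sets its final value does not know the arm. The two assistants may be fully blinded, but when they disagree the decision passes to someone with a working role in one arm. These are the records on which trained readers differ, so they leave the most room for judgement. A tendency to resolve them in favour of the podcast arm, even an unconscious one, would be detection bias in part of the primary outcome. The trial report would nonetheless describe that outcome as assessed under double blinding.

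**Working it through.** There is no figure in the plan to reproduce. The check sets the roles side by side and then bounds the effect of a single reading.

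**1. Can the investigator identify the arm?** Voice feedback exists only in the experimental arm (Table 3), and the investigator coordinates the replies to it (Section 3.5.1). Anyone whose feedback reaches the investigator is therefore an experimental participant. Three rounds are planned for each, all complete by Week 10 and so before T1 at the end of the 3-month intervention. Control status can be inferred by elimination, though imperfectly, because an experimental participant who submits nothing looks the same.

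**2. Does the investigator set outcome values?** Yes, for discrepant records only (Section 3.7.2). The article describes no removal of participant code or arm before a record is passed on.

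**3. Is there room for judgement?** Yes. The review is manual, done in duplicate and scored for agreement. The recheck rule depends on whether carbohydrate was taken before the second reading, and the article does not say that this is stored with the readings. The article does not tie the investigator's verification to the recheck rule specifically, but a dispute over that rule is one that could reach the investigator.

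**4. Which measures?** A recheck kept or dropped changes the denominator of the in-range percentage and, if it lies in range, the numerator. The first low is always kept, so the hypoglycaemic count changes only if the recheck is itself low. The hyperglycaemic count is less obviously exposed. HbA1c comes from electronic medical records and is not described as passing through this step.

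**5. Which assessments?** T0 precedes randomisation (Section 3.1), and envelopes are opened only after baseline assessment (Section 3.4). That leaves T1, T2 and T3: three of four.

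**6. Effect of one reading.** Section 3.7.2 gives 2 to 5 tests a day and a 3-month download. Taking 3 months as 90 days (an assumption), the number of readings n is 2 × 90 = 180 to 5 × 90 = 450. Let k be the number in range.

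- Reclassifying one reading changes k/n by 1/n.
- Dropping one in-range reading changes it by (n − k)/[n(n − 1)], which is at most 1/n.
- Dropping one out-of-range reading changes it by k/[n(n − 1)], also at most 1/n.

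The bound is 1/180 = 0.56 percentage points to 1/450 = 0.22 percentage points per disputed reading, per participant and assessment. The article does not say how many readings would be disputed, so no total follows.

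**The case against.** **The investigator is never listed as blinded.** Section 3.4 claims blinding for data collectors and participants only. This stands: a reader might infer that the article contradicts itself, but the wording on data collectors is not literally breached. The point remains that assessment of a value is not blind if an unblinded person decides it.

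**The exposure is narrow.** Only disputed records are affected, the recheck rule is stated in advance, and HbA1c, on which the sample size rests, is untouched. All of this stands and limits the weight of the point.

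**RA2.** A reader might infer from the body of Table 4 that RA2 also knows allocation while handling glucose data. The documents do not support this. No passage says RA2 is told the allocation, and Section 3.7.2 does not say which assistants review the readings. The footnote fits a respective reading, with RA2 auditing RA1's data collection and RA4 auditing RA3's interventions. Taken literally, the body would have RA1 delivering interventions, which is not RA1's role. What remains is loose wording, repeated in the delivery row, that should be reconciled.

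**Weekly discussions.** Table 4 lists weekly discussions with the investigator for all four assistants, over logs of data collection and of intervention. A reader might infer joint meetings at which arm is revealed. Neither is stated, and the manuals in File S1 are not shown.

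**Conclusion.** The point holds for the principal investigator. For disputed self-monitored glucose records at T1 to T3, the final value is set by someone able to recognise experimental participants. The in-range percentage, and possibly the event counts, are to that extent not assessed blind, despite the double-blind label.

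This is a gap in the blinding scheme rather than a literal contradiction, and it does not show that any result would be biased. Its size is unknown: each disputed reading is worth at most about 0.2 to 0.6 percentage points of one participant's in-range percentage, and the number of such readings is not given. Baseline and HbA1c are not affected.

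The conclusion assumes that a disputed record reaches the investigator in a form that can be linked to the participant, since the article describes no masking. If an unshown manual already strips identity from these records, the gap is closed and only needs stating. The Table 4 wording on RA2 is a matter for clarification, not evidence of unblinding.

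**What to change.** 1. In Section 3.7.2, state that discrepant records go to the resolver as reading sequences without participant code or arm, or that existing staff with no intervention role settle them. If neither is done, do not describe the self-monitored glucose outcomes as blinded.
2. Reconcile the body of Table 4 (treatment-design and delivery rows) with its footnote, so that RA2 audits RA1's data collection only and RA4 audits RA3's interventions.
3. State that intervention logs that identify the arm are kept out of discussions with data-collection staff.

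A script that applies the recheck rule to time-stamped readings would not replace step 1. The rule depends on carbohydrate intake, which the article does not say is recorded with the readings, so a script would substitute a time window for the stated rule.

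The cost is minor extra data preparation and some rewording. No extra staff are needed, and the endpoints, intervention and sample size do not change.

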#### 3.7.3. Secondary Outcome: Well-Being—Emotional Distress

This outcome will be measured using the Chinese version of the Diabetes Distress Scale. Three subscales with 15 items will be used: emotional burden, physician-related distress, and regimen-related distress; the fourth subscale, interpersonal distress, will measure “Relationship Comfort: Diabetes-Related Interpersonal Distress” in this study. Total scores range from 15 to 60, with higher scores indicating more significant distress [72].

#### 3.7.4. Secondary Outcome: Mastery—Diabetes Knowledge, Self-Care Behaviors, and Self-Management Confidence

Diabetes knowledge will be measured using the Chinese version of the Diabetes Knowledge Questionnaire comprising 24 items. Participants must answer “Yes,” “No,” or “I don't know” for each item and are awarded 1 point for each correct answer. Total scores range from 0 to 24 points, with higher scores indicating more knowledge of diabetes [73]. The original questionnaire was developed for Type 2 diabetes, but Items 6 and 13 have been modified for relevance to T1D. Item 6, “If I have diabetes, my children are very likely to have diabetes,” is changed to “false,” and Item 13, “Medication therapy controls diabetes better than appropriate diet and exercise,” is changed to “true.” These modifications have been validated in T1D patients [57].

Self-care behaviors will be measured using the Diabetes Self-Care Behavior Scale comprising 39 items under seven dimensions: medication management (insulin injection), healthy eating (diet control), blood glucose monitoring (self-monitoring), physical activity (regular exercise), problem-solving, risk reduction, and healthy coping (psychosocial adaptation and stress management). Total scores range from 39 to 195, with higher scores indicating superior self-care [74].

Self-management confidence will be measured using the Chinese version of the Perceived Diabetes Self-Management Scale comprising 24 items. Total scores range from 8 to 40, with higher scores indicating higher confidence in diabetes self-management [75].

#### 3.7.5. Secondary Outcome: Relationship Comfort—Diabetes-Related Interpersonal Distress and Family Conflict

Diabetes-related interpersonal distress will be measured using the Chinese version of Interpersonal Distress, a subscale of the Diabetes Distress Scale with three items: “Feeling that friends or family are not supportive enough of my self-care efforts (e.g., planning activities that conflict with my schedule, encouraging me to eat the “wrong” foods),” “Feeling that friends or family do not appreciate how difficult living with diabetes can be,” and “Feeling that friends or family do not give me the emotional support that I would like.” Total scores range from 1 to 12, with higher scores indicating more significant diabetes-related interpersonal distress [72].

Family conflict will be measured using the Diabetes Family Conflict Scale-Revised comprising 19 items under two dimensions: direct and indirect management tasks. Direct management tasks refer to conflicts directly related to diabetes care, such as “During the past month, I have argued with my parent(s) about the results of blood sugar monitoring.” Indirect management tasks refer to conflicts not directly related to diabetes care, such as: “ During the past month, I have argued with my parent(s) about telling friends about diabetes.” Total scores range from 19 to 57, with higher scores indicating more significant conflict [76].

### 3.8. Statistical Analysis

Descriptive statistics such as frequency distribution, percentage, mean, standard deviation, and maximum/minimum scores will be utilized to characterize the subjects' demographics, disease characteristics, outcome variables at enrollment, and podcast usage. The efficacy of the intervention will be assessed using generalized estimating equation (GEE) modeling, which accommodates repeated measurements and deals with missing data effectively, following the intention-to-treat principle.

GEE will evaluate differences in outcome variables between experimental and control groups over time. Linear GEE models will be applied for all the continuous outcomes. The models will include fixed effects for the group (experimental vs. control), time (baseline, postintervention, and 3 and 6 months postintervention), and their interaction. The working correlation structure will be selected based on the quasi-likelihood under the independence model criterion [77]. Statistical significance will be determined at *p* < 0.05. All analyses will be conducted using IBM SPSS 26.0 for Windows.

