#### 3.3.2. Sample Size Calculation

Few studies have explored podcast-based interventions for chronic diseases or illnesses in adolescents. As podcasting is a technology-based intervention method, results from our prior study of Healthcare CEO App [57] were used for sample size calculation. Effect sizes were calculated using Cohen's *d*. For groups of 19 participants each, the mean HbA1c for the experimental vs control group at 3, 6, and 9 months postintervention was 7.93 ± 1.36 versus 8.69 ± 2.40, 8.30 ± 1.29 versus 8.82 ± 2.69, and 8.24 ± 1.58 versus 8.87 ± 2.72, respectively, yielding an effect size of 0.38, 0.26, and 0.32, respectively.

Using G-Power 3.1.9.4 software, the required sample sizes were calculated for each group across the three time points as 18, 38, and 26 participants, respectively. Assumptions included two groups with four repeated measures, *α* set at 0.05, power at 0.80, and a correlation coefficient of 0.5. No participants withdrew from our prior study [57]. However, considering a conservative dropout rate of 12% based on similar online intervention studies with a 6-month follow-up period [64], the number of participants was increased to 21, 44, and 30 per group. The maximum sample size calculated based on the smallest effect size at T2 was chosen. Therefore, the total sample size will be 88 participants.

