#### 3.5.2. Active Control Group: Sham Treatment

Our previous study demonstrated that e-books did not have a significant impact on glycemic control (HbA1c: 8.30 ± 1.29 vs. 8.82 ± 2.69, *p* = 0.477), diabetes knowledge (16.59 ± 3.26 vs. 15.42 ± 3.85, *p* = 0.336), self-care behaviors (152.94 ± 13.38 vs. 155.95 ± 14.56, *p* = 0.525), self-management confidence (29.82 ± 4.30 vs. 27.63 ± 5.82, *p* = 0.212), or interpersonal distress (11.00 ± 5.01 vs. 10.53 ± 6.54, *p* = 0.811) after 6 months in our prior trial [57]. Therefore, the active control group will receive the e-book “Transitioning from Adolescence to Early Adulthood: The Ins and Outs of Type 1 Diabetes,” compiled from the Healthcare CEO app collection, as a sham treatment. This title and content indicate its suitability as a minimally active control that is thematically relevant [66, 67]. The topics in the e-book include (1) diabetes knowledge, (2) how to manage your blood sugar, (3) eating and exercising well, (4) healthy interpersonal relationships, (5) parent–child harmony, and (6) you are not alone. Each unit includes recommended readings, such as “Needles” and “My Life Is Not Controlled by Diabetes.” Although parts of the themes are similar, the e-book is simplified to 600–800 words of pure text per unit, lacking T1D patient experience sharing and interactive engagement. Participants in the active control group will not be reminded to read the e-book, no additional interventions or consultations will be provided, and no follow-up calls will be made during the intervention. After the study, participants in the active control group will be offered the opportunity to listen to all podcast episodes and receive the same incentives as the experimental group, if desired. The intervention characteristics of the experimental and active control groups are presented in Table 3.

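### Unweighted GEE is said to handle missing data effectively, but with the working correlation left to QIC this is not assured if dropout depends on earlier outcome values

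*Protocol article*

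**What the plan says.** Section 3.8 assesses efficacy with GEE, "which accommodates repeated measurements and deals with missing data effectively, following the intention-to-treat principle". On the model it says: "The models will include fixed effects for the group (experimental vs. control), time (baseline, postintervention, and 3 and 6 months postintervention), and their interaction". No other covariates are named. On the within-person structure: "The working correlation structure will be selected based on the quasi-likelihood under the independence model criterion". The section gives no missing-data assumption, weighting or imputation, so the quoted sentence is the article's only justification for how missing outcomes are treated.

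Section 3.3.2 plans for 12% dropout. It says that the prior app trial had 19 participants in each group and that "No participants withdrew from our prior study". Section 3.5.2 prints that trial's 6-month results for five outcomes, for example "diabetes knowledge (16.59 ± 3.26 vs. 15.42 ± 3.85". Its HbA1c pair (8.30 ± 1.29 and 8.82 ± 2.69) is the one that Section 3.3.2 labels experimental versus control.

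**The concern.** Ordinary GEE uses whatever observations are available. Under an independence structure with group, time and their interaction, the fitted value for each arm and visit is the mean of the people still observed there. If people with higher HbA1c at T1 are more likely to be missing later, and this happens more in one arm, that arm's later means are too low and the group-by-time contrast is wrong. The robust standard error does not correct this.

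A working correlation close to the truth largely removes the problem, because each missing person's earlier values then inform the later mean. The plan gives up that safeguard by leaving the choice to a data-driven criterion. A reader told that missing data are handled effectively under intention to treat would not know that this depends on which structure is selected.

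**Working it through.** **1. The plan's loss rate.** Section 3.3.2: 38 / 0.88 = 43.2, rounded up to 44 per group, total 88. The 12% allowance reproduces. If all of it fell in one arm, that arm would lose 0.12 × 88 / 44 = 24%.

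**2. Bias under independence.** Suppose there is no true effect, the control arm is complete, and experimental participants drop out after T1 with log-odds linear in standardised T1 HbA1c (Z). Let π be the experimental-arm loss, σ the SD and r the T1–T3 correlation. Then

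bias at T3 = −r σ × [π / (1 − π)] × E(Z | dropped).

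Inputs: r = 0.5 is the sample-size correlation in Section 3.3.2, and 0.7 is an assumed alternative. σ = 2.0 is assumed; the 6-month SDs printed there pool to √[(1.29² + 2.69²)/2] = 2.11. The dropout odds ratio per SD is assumed to lie between 1.65 and 4.48.

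| Loss π | Odds ratio | E(Z given dropped) | r | Bias (HbA1c points) |
|---|---|---|---|---|
| 2/19 = 10.5% | 1.65 | 0.437 | 0.5 | −0.051 |
| 2/19 = 10.5% | 4.48 | 1.083 | 0.5 | −0.127 |
| 12% | 1.65 | 0.428 | 0.5 | −0.058 |
| 12% | 4.48 | 1.051 | 0.5 | −0.143 |
| 24% | 4.48 | 0.845 | 0.5 | −0.267 |
| 24% | 4.48 | 0.845 | 0.7 | −0.374 |

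Example, fourth row: 0.5 × 2.0 × (0.12/0.88) × 1.051 = 0.143. Simulations of the same setting put the lower end at 0.04 to 0.05.

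The 6-month planning difference is 8.82 − 8.30 = 0.52 points. So 0.05 to 0.14 is about 10 to 27% of it, and 0.37 is about 71%.

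**3. The same dropout with other structures.** With the correct within-person correlation the bias is about zero. With an exchangeable structure it is about zero when the truth is exchangeable. When the truth is AR(1) it stays below about 0.08, the largest value occurring at 24% loss and the strongest dependence.

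**4. When there is no bias.** Under independence the bias is also about zero if dropout is completely random, or if the same rate and mechanism apply in both arms. Unequal loss alone does not create bias.

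**5. The prior trial's group sizes.** Pooled two-sample t-tests from the printed 6-month means and SDs:

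| Outcome | Printed p | 19 vs 19 | 17 vs 19 |
|---|---|---|---|
| HbA1c | 0.477 | 0.452 | 0.473 |
| Knowledge | 0.336 | 0.319 | 0.335 |
| Self-care | 0.525 | 0.511 | 0.524 |
| Confidence | 0.212 | 0.195 | 0.212 |
| Interpersonal distress | 0.811 | 0.805 | 0.812 |

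Allowing for rounding of the means and SDs, 17 vs 19 reproduces all five p-values and 19 vs 19 reproduces none.

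The four questionnaire scores are sums of whole numbers, so each mean must be an integer divided by n. The experimental means fit 17: 282/17 = 16.59, 2600/17 = 152.94 and 507/17 = 29.82. None of these three is attainable with 19. The control means fit 19: 293/19 = 15.42, 2963/19 = 155.95, 525/19 = 27.63 and 200/19 = 10.53. Among all pairs from 12 to 19 per arm, only 17 versus 19 passes every check.

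**The case against.** The other side has a good case, and much of it stands.

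- **GEE is not the fault in itself.** It is tempting to say that GEE is valid only under completely random dropout and must be biased here. That is too strong. A linear GEE with a reasonable non-independence structure is close to unbiased when dropout depends on observed values, and Section 3.8 does not choose independence. In 100 simulated trials of 44 per arm, QIC preferred exchangeable to independence in 70 and independence in 30. The risk is real but partial.
- **The large figure is a worst corner.** The 0.37 needs 24% loss in one arm and none in the other, an odds ratio of 4.48 per SD, r = 0.7, and independence selected. In the central range, with 38 and 44 observed, the standard error of the change contrast is √(4/38 + 4/44) = 0.44, so a bias of 0.05 to 0.14 is about 0.11 to 0.33 standard errors.
- **The direction is assumed.** A reader might infer that losses will flatter the podcast. The article does not support this. HbA1c comes from medical records (Section 3.7.2), so stopping listening does not by itself remove it. The experimental arm gets reminders and a telephone call (Section 3.6.1), and controls get neither (Section 3.5.2). Greater loss in the control arm is as plausible.
- **The prior trial does not show differential dropout.** Two of 19 against none of 19 gives a Fisher exact p of 0.49. It concerns a different intervention and says nothing about whether loss depended on HbA1c. Missing 6-month values are not necessarily withdrawals, so the no-withdrawal statement need not be false.
- **Details may sit in an analysis plan.** Sensitivity analyses may well be there, and their absence is not criticised. The article, however, makes a positive claim and commits to QIC selection, and both stand as written.

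**Conclusion.** The concern holds in a limited form. The claim in Section 3.8 is unqualified and is not generally true of unweighted GEE, and selection by QIC leaves open the one structure under which the weakness matters most. If independence is selected and dropout both depends on T1 HbA1c and differs by arm, expect a bias of roughly 0.05 to 0.14 points at loss rates near those planned, with 0.37 as an upper extreme. These sizes rest on the assumed SD, correlation and dropout strength, and the sign on which arm loses its worse-controlled participants. The article does not establish that such dropout will occur. The change is worth making because it is cheap, not because bias has been shown to be likely.

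The mismatch between Sections 3.3.2 and 3.5.2 is a separate reporting discrepancy. It shows that some 6-month data were missing in the prior trial, and no more.

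**What to change.** 1. Delete the statement that GEE deals with missing data effectively, and state the missing-at-random assumption on which the analysis relies.
2. Make the primary analysis of HbA1c and the continuous scores a REML mixed model for repeated measures. Keep group, time and their interaction, and fix an unstructured covariance in advance. The MIXED procedure of the software named in Section 3.8 fits it.
3. If GEE is kept, at minimum pre-specify a non-independence working correlation in place of QIC selection.
4. Reconcile Section 3.3.2 (19 per group, no withdrawals) with the 6-month figures in Section 3.5.2, giving the number analysed per arm and the reason for any missing values.

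The cost is wording only: recruitment, data collection and software are unchanged. The mixed model adds a normality working assumption. Neither option protects against dropout that depends on unseen values: at 12% experimental-arm loss and r = 0.5, dropout driven by the T3 value itself gave a bias of 0.12 to 0.29 points under independence.
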